#### 6.2.11. Cognition

Cognitive function is assessed at baseline (both computer battery and non-computer based battery) and at 18 (computer battery only), 24-months (non-computer based battery only), and at the PIV (non-computer based battery only) visits in all participants. Participants who are unable to take the battery components at 18 or 24 months will be allowed to take them at the 30 month visit. The LIFE Study cognition assessment battery measures were selected because they have been used often in research examining aging and cognitive disorders and have been improved by either cognitive or physical activity interventions. As described in Section 3.3, the DSST and the HVLT are the two cognitive measures upon which the cognition outcome in LIFE is powered and will be assessed in the following manner:

1. **Digit Symbol Substitution Test (DSST)** is a measure of attention and perceptual speed in which participants are given a series of numbered symbols and then asked to draw the appropriate symbols below a list of random numbers. The score is the number of correctly made matches in 2 minutes (120 seconds).
2. **The Hopkins Verbal Learning Test (HVLT)** is a 12-item list learning and memory test designed for brief, easy administration with proven participant tolerability in a variety of populations. The HVLT requires the participant to listen to a list of 12 words and repeat as many as possible. The task is repeated twice, for a total of three trials. Approximately 20 minutes later, s/he is asked to recall as many words as possible. The participant is also presented a yes/no delayed recognition trial consisting of a randomized list that includes the 12 target words and 12 non-target words, six of which are drawn from the same semantic categories as the targets. Scores for immediate recall (total of three trials), delayed recall, and recognition are calculated into a summary score.

In addition:

3. **The Modified Mini-Mental Status Exam (3MSE)** will be administered as a test of global cognitive function which assess a broad variety of cognitive measures. This is an expanded 100 point version of the original Folstein MMSE and has been used in large epidemiological studies and clinical trials to effectively screen for persons experiencing impaired cognition and estimate incident Mild Cognitive Impairment (MCI) or dementia (see below).

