4. **The Modified Rey-Osterrieth Complex Figure (Rey-O)** copy and immediate recall will be administered as a measure of visuospatial skills. The Rey-O has published normative data and there are standard qualitative scoring schemes that provide important information about the nature of underlying cognitive impairment.

The final components of the cognitive battery will be a computer-based battery of tests focused on elements of executive function:

5. **Eriksen flanker task** measures response inhibition. Participants are presented with an arrow facing either right or left and are asked to press a key indicating its direction. The target displays can be neutral (no flankers), congruent (flanker arrows point in the same direction as the target arrow), or incongruent (the flanker arrows point in the opposite direction).
6. **N-Back Test** measures working memory. Participants see individual letters at a 2-second rate on a computer screen and are asked to indicate whether the presented letter is the same as the nth back letter, with n equal to 1 and 2.
7. **Task Switching** measures attentional flexibility. Participants are asked to quickly alternate between performing two different tasks, which requires executive function to reconfigure the cognitive system each time the task demands shift. They will be shown single digit numbers and asked to determine if they are odd or even, which will alternate with presentation of single letters for which they will have to indicate whether the letter is a consonant or vowel.

Participants with known dementia or who score below education-based cutoffs on the 3MSE will be excluded from the LIFE trial during the screening visit (see 4.2.1). In order to classify cognitive status on all participants enrolled at baseline, those who score 76 - 88 (English speaking non-African American) or 70-88 (African American and Spanish speakers) on the 3MSE will need an assessment of daily functioning with regard to cognitively demanding tasks. Thus, we will administer the **Functional Activities Questionnaire (FAQ)** to a proxy (family member, close friend or caregiver). The FAQ is a brief, 10 item questionnaire, that has been validated for the purposes of ascertaining the impact of cognition on important daily functions. Results from the FAQ in combination with the cognitive tests will be used to classify the cognitive status of all participants at baseline.

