**(b) A composite measure** derived from the cognitive assessment battery (DSST, HVLT, Flanker, N-back and Task Switching), excluding the 3MSE, will be standardized and averaged to form a single composite score for additional analysis as a tertiary outcome.

**(c) Short Physical Performance Battery (SPPB).** The SPPB, originally developed for the Established Populations for the Epidemiologic Study of the Elderly (EPESE) is a brief performance battery based on timed short distance walk, repeated chair stands and balance test (as described by Guralnik et al.)

**(d) Sleep-Wake Disturbances** will be evaluated with four validated instruments: Epworth Sleepiness Scale (ESS), Insomnia Severity Index (ISI), Pittsburgh Sleep Quality Index (PSQI), and Berlin Questionnaire (BQ).

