**Tertiary aim #2** will be to explore the effects of the intervention on composite measure of the cognitive assessment battery. We will also construct a composite measure to include all components of the Cognitive Assessment Battery (but not the 3MSE, which is used as to screen participants for MCI/D classification). For this composite measure of cognitive performance we will z-transform each score by dividing its difference from the baseline mean by the baseline standard deviation, and then will average the z-transformed measures. This approach, rather than adopting weighted averages, provides slightly greater emphasis on executive function.] The relative effect of the PA intervention on this composite will be assessed with analyses of covariance applied to the measures collected at Year 2, with the baseline composite included as a covariate. Differences between intervention arms for each individual test that contributes to the composite measure will be described. A similar approach will be used to assess the impact of the intervention on executive functions using a composite score for the three executive function tests (Flanker, N-back and Task Switching)

**Tertiary aim #3** will be to assess the effects of the interventions on the SPPB score and 400 m walk speed within ethnicity/race, gender and baseline physical performance subgroups. Repeated measures analysis of covariance techniques for continuous outcomes (such as described for ADLs) will be used to explore these effects (mixed effects models). Estimates of the intervention effect will be obtained within these subgroups and formal tests of interactions between intervention and subgroup variables will be performed. Forest plots will be used to graphically display the results of these subgroup analyses.

**Tertiary Aims #4** will be assessed using a Cox proportional hazards model, stratified by Field Center and gender. Failure time is measured from the time of randomization to the first sleep-wake disturbance.

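### The tertiary cognitive composite is analysed at Year 2, but three of its tests (the computer-based executive tests) are scheduled at month 18 and not at month 24, and its two component lists disagree

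*Protocol*

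**What the plan says.** **Analysis rule.** Protocol section 12.2, Tertiary aim #2, standardises each test score to its baseline mean and standard deviation, averages the results, and assesses the intervention effect on the composite by "analyses of covariance applied to the measures collected at Year 2, with the baseline composite included as a covariate". It then applies what it calls a similar approach to "a composite score for the three executive function tests (Flanker, N-back and Task Switching").

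**Content of the composite.** Section 10.3.6(b) describes a measure "derived from the cognitive assessment battery (DSST, HVLT, Flanker, N-back and Task Switching), excluding the 3MSE". Section 12.2 instead says "We will also construct a composite measure to include all components of the Cognitive Assessment Battery", leaving out only the 3MSE.

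**Schedule.** Section 6.2.11 introduces the three executive tests with "The final components of the cognitive battery will be a computer-based battery of tests focused on elements of executive function". After baseline it sets cognitive testing "and at 18 (computer battery only), 24-months (non-computer based battery only), and at the PIV (non-computer based battery only) visits in all participants". A participant who cannot take a component at month 18 or 24 may take it at month 30. Section 10.1, Table 10.1 and the table's footnote give the same visits.

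**The concern.** The analysis rule fixes a visit, a model, a covariate and a method of standardisation. The visit is one at which the protocol's own schedule does not collect three of the tests being averaged. Whoever carries out Tertiary aim #2 would have to choose between dropping the executive tests, bringing in scores from another visit, and moving the time point. Each choice gives a different outcome variable, and nothing stops the choice from being made after data have been seen.

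The choice also affects what the composite measures. Section 12.2 justifies the unweighted average on the ground that it leans slightly towards executive function. A strict Year 2 composite contains none of the computer-based executive tests, so it would not do what that rationale claims.

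**Working it through.** No power or sample-size figure is at issue: Table 3.3.2 covers only DSST and HVLT. The check sets the analysis rule against the schedule and counts components.

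**Step 1. What Year 2 means.** Section 3.3 says the DSST and HVLT data are collected at baseline and year 2. Section 12.2, Secondary aim #1, speaks of baseline and 2-year visits. Section 10.3.1 gives the same assessments as baseline and the 24-month follow-up. Outside cognition, the quality-of-life measures that section 6.2.12 sets at years one and two are marked at F12 and F24 in Table 10.1. Year 2 is therefore the month-24 visit.

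**Step 2. Where each test is scheduled** (sections 6.2.11 and 10.1, Table 10.1 and its footnote).

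| Test | Baseline | Month 18 | Month 24 | Month 30 |
|---|---|---|---|---|
| DSST | yes | no | yes | make-up only |
| HVLT | yes | no | yes | make-up only |
| Modified Rey-O | yes | no | yes | make-up only |
| Flanker | yes | yes | no | make-up only |
| N-back | yes | yes | no | make-up only |
| Task Switching | yes | yes | no | make-up only |

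In Table 10.1 the computer battery (EPrime) is marked at SV2, F18 and F30, and the F24 cell is empty.

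**Step 3. Components scheduled at Year 2.**

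- Overall composite, five-test list in 10.3.6(b): 2 of 5 present (DSST, HVLT); 5 − 2 = 3 absent by design.
- Overall composite, section 12.2 list read as adding the Modified Rey-O: 3 of 6 present; 6 − 3 = 3 absent by design.
- Executive composite, if Year 2 carries over to it: 0 of 3 present.

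At month 18 the five-test list has 3 of 5 and the executive composite 3 of 3. No scheduled follow-up visit gives all five tests to all participants, since month 30 serves only those who missed a battery.

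**Step 4. Weight on the computer-based executive tests.** With equal weights, their share is 3/5 = 60% in the five-test composite and 3/6 = 50% in the six-test one. At Year 2 the shares are 0/2 and 0/3, which is 0% in both cases.

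**Step 5. The component lists.** The two sections differ by at least the Modified Rey-O. Section 10.1 also places Category Fluency, Boston Naming and Trails A and B in the battery at month 24. These have no baseline administration, so they cannot be standardised to a baseline mean and standard deviation as section 12.2 requires. The phrase in section 12.2 therefore cannot be applied at its widest.

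**Step 6. Spacing if visits are combined.** Computer tests at 18 and paper tests at 24 are 24 − 18 = 6 months apart. With computer tests made up at 30 and paper tests at 24, the gap is again 30 − 24 = 6. With computer tests at 18 and paper tests made up at 30, it is 30 − 18 = 12. If both are made up at 30, it is 0.

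**The case against.** The best defence is that this is a loose phrase in an exploratory aim. The composite is tertiary, has no power calculation and no share of alpha, and all the tests are collected anyway. A statistical analysis plan could assign the visits in one line. The limited reach is a fair point. But the protocol did not leave the visit open. It stated one, and that visit contradicts its own schedule.

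A second defence reads Year 2 as the second year of follow-up, which would take in month 18. The usage in sections 3.3, 6.2.12, 10.3.1 and 12.2 does not support that reading.

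The documents do not support several stronger readings that a reader might infer:

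- *That neither analysis can be run.* The Year 2 time point is stated for the overall composite. It reaches the executive composite only through the reference to a similar approach, which could mean the same standardisation and model at another visit. All participants are scheduled for the executive tests at baseline and month 18, so that analysis is feasible. The overall analysis could also be run on a reduced set of tests, although that is not the composite the protocol defines.
- *That the Year 2 composite merely repeats the two secondary cognitive outcomes.* This holds under the list in 10.3.6(b). Under section 12.2 the Modified Rey-O would also be present.
- *That averaging would cancel a benefit because some scores run in the opposite direction.* The protocol does not say how the computer tests are scored, and orienting scores before averaging is a detail that a statistical analysis plan can supply. No finding rests on it.

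**Conclusion.** The inconsistency is real. Applied as written, the Year 2 rule cannot produce the composite in section 10.3.6(b): 3 of 5 listed tests (3 of 6 with the Modified Rey-O) are absent by design for every participant, and the intended lean towards executive function is lost. The executive composite has no scheduled Year 2 data, on the condition that the similar approach includes the time point. Separately, sections 10.3.6(b) and 12.2 define the overall composite differently.

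The conclusion rests on Year 2 meaning the month-24 visit, which the protocol's own usage supports, and on the schedule, which is consistent wherever it gives the visit for the computer battery. The consequence is confined to exploratory tertiary outcomes. The correction is worth making because it costs little and removes a choice that could otherwise be made after seeing data.

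**What to change.** In section 12.2, Tertiary aim #2, name the visit for each component:

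- Analyse the executive composite (Flanker, N-back, Task Switching) at month 18, with month-30 make-up scores allowed.
- Build the overall composite from month-24 DSST and HVLT and month-18 computer tests, with month-30 make-up scores allowed for either group.
- Give one identical component list in sections 10.3.6(b) and 12.2, and say explicitly whether the Modified Rey-O is in it. If it is, take it from month 24.

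No visit, test or procedure changes; the data are already scheduled.

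The downside is that the overall composite mixes visits usually 6 months apart, and up to 12 months apart when make-up visits are used. Use of make-up visits may differ by arm, so the spacing need not be balanced. Reporting the number of make-up scores by arm would show whether this matters. Separate composites by visit would avoid the mixing but would give up the single overall score that section 10.3.6(b) calls for.

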###### Tertiary hypotheses: Compared with SA, the PA program

- Reduces the risk of the combined outcome of all-cause mild cognitive impairment or dementia (MCI/D);
- Improves performance on a composite measure of cognitive function;
- Improves physical performance within subgroups defined on the basis of ethnicity/race, gender and baseline performance;
- Results in improvements in measures of physical performance and walking speed that vary with the amount of intervention received;
- Improves sleep-wake disturbances and leads to a lower incidence of sleep-wake disturbances;
- Reduces dyspnea and improves ventilatory capacity;
- Reduces the risk of hospital admissions for exacerbation of airway disease (asthma, bronchitis, emphysema, &/or COPD) or pneumonia; and

- Reduces the risk of combined cardiovascular (CVD) events including:
  - Myocardial infarction (MI),
  - Angina requiring hospitalization,
  - Any stroke (ischemic or hemorrhagic),
  - Transitory ischemic attack (TIA) requiring hospitalization,
  - Hospitalization for carotid artery disease,
  - Hospitalization for congestive heart failure (CHF),
  - Hospitalization for peripheral artery disease (PAD) or outpatient revascularization for PAD,
  - Ruptured abdominal aortic aneurism (AAA), and
  - CVD death.

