Calculations were similar as for CVD event power. Because of the lower expected event rates (even with larger assumed effect sizes), the power is considerably lower. Power for ventilatory capacity is presented in Table

3.3.6. For simplicity and to be conservative, we have assumed an analysis of covariance model with adjustment for baseline but have not accounted for multiple follow-up measurements. A mixed model will ultimately be used to account for this correlation. Assumed standard deviations were 0.57 for FEV1 and 0.66 for FVC. With effect sizes of 0.05 units, there is modest power, but effect sizes of 0.1 there is substantial power. Power for sleep wake disturbances are presented in Table 3.3.7. As above, we assume 8%/year loss to follow-up. With a 5%/year event rate and a 30% effect (hazard ratio of 0.7), we would have 59% power to detect an effect using a two-sided test at the 5% level.

| Table 3.3.4. CVD Event Power |                         |                         |                         |
|------------------------------|-------------------------|-------------------------|-------------------------|
| Effect Size                  | 2%/yr SA Incidence Rate | 4%/yr SA Incidence Rate | 6%/yr SA Incidence Rate |
| 30%                          | 29%                     | 51%                     | 67%                     |
| 40%                          | 49%                     | 78%                     | 91%                     |
| 50%                          | 70%                     | 94%                     | 99%                     |

| Table 3.3.5. Hospitalized Pulm Event Power |                           |                           |                         |
|--------------------------------------------|---------------------------|---------------------------|-------------------------|
| Effect Size                                | 0.1%/yr SA Incidence Rate | 0.5%/yr SA Incidence Rate | 1%/yr SA Incidence Rate |
| 40%                                        | 7%                        | 16%                       | 28%                     |
| 50%                                        | 9%                        | 24%                       | 42%                     |
| 60%                                        | 11%                       | 34%                       | 59%                     |

| Table 3.3.6 Ventilatory Capacity Power |             |      |     |

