#### **6.2.16. Sleep-Wake Disturbances**

As a tertiary outcome, Sleep-Wake Disturbances will be evaluated with four validated instruments: Epworth Sleepiness Scale (ESS), which assesses perceived daytime drowsiness during several different activities, Insomnia Severity Index (ISI), which assesses insomnia symptoms, Pittsburgh Sleep Quality Index (PSQI), which assesses perceived sleep quality and disturbances, and Berlin Questionnaire (BQ), which assesses the clinical risk for obstructive sleep apnea. In addition to these instruments, two additional questions will be administered regarding napping behavior and the use of caffeine and energy drinks. These sleep instruments and the additional two questions will be completed at SV2 and at the 6, 18 and 30 month clinic visits.

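### The sleep-wake aim claims improvement and lower incidence, but its one time-to-first-disturbance model estimates no improvement in scores and states no disturbance-free risk set, and its power table allows for no baseline cases

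*Protocol*

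**What the plan says.** - **Hypothesis (Protocol 3.1.2, tertiary).** The program "Improves sleep-wake disturbances and leads to a lower incidence of sleep-wake disturbances". These are two claims.
- **Analysis (12.2, Tertiary Aims #4).** The aim "will be assessed using a Cox proportional hazards model, stratified by Field Center and gender". The time scale and event are then given: "Failure time is measured from the time of randomization to the first sleep-wake disturbance". Nothing else is planned for sleep. The text does not say who is in the risk set.
- **Data (6.2.16).** "Sleep-Wake Disturbances will be evaluated with four validated instruments": ESS, ISI, PSQI and the Berlin Questionnaire. Timing: "These sleep instruments and the additional two questions will be completed at SV2 and at the 6, 18 and 30 month clinic visits". A baseline value and up to three repeat scores therefore exist.
- **Eligibility (4.1.2 and 4.2).** No inclusion, exclusion or temporary exclusion criterion concerns sleep.
- **Power (3.3 and Table 3.3.7).** "With a 5%/year event rate and a 30% effect (hazard ratio of 0.7), we would have 59% power". The significance level is two-sided 0.05, and loss to follow-up is taken as 8% per year. Baseline prevalence is not mentioned.
- **Comparable outcomes in the same protocol.** For mild cognitive impairment or dementia (MCI/D), section 3.3 takes 10% baseline prevalence into the power calculation, and section 12.2 analyses conversion from baseline. For ADL disability and for FEV1/FVC, section 12.2 plans mixed models adjusted for the baseline level.

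**The concern.** A time-to-first-event model suits the primary outcome because everyone must complete the 400 m walk to enter, so nobody starts with the event. Sleep disturbance has no such entry condition, and some participants can be expected to have it at SV2.

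Two things follow. First, the improvement half of the hypothesis has no analysis that estimates it. A score that falls without crossing the event threshold leaves no trace in a time-to-first-disturbance model. Second, the incidence half depends on whether baseline cases are in the risk set, which section 12.2 leaves open. If they are in, the hazard ratio blends new onset with persistence of old disturbance. If they are out, fewer than 1,600 are at risk and the printed power is too high. At stake is whether this aim can answer the question it poses, and whether its power figure describes the analysis that will be run.

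**Working it through.** **Inputs from the protocol.** N = 1,600 in two nearly equal arms (5.1, 6.4.2); follow-up 23 to 42 months with uniform recruitment (3.3); loss 8% per year; control rate 5% per year; hazard ratio 0.70; two-sided 0.05. **Not in the protocol:** baseline prevalence and persistence of disturbance. Both are assumed below over a range.

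**Step 1: reproduce the stated power.** Take exponential onset at hazard λ, loss hazard μ = −ln(0.92) = 0.0834, and follow-up T uniform from 1.917 to 3.5 years. Expected events per arm are n × mean over T of λ/(λ+μ) × [1 − exp(−(λ+μ)T)].

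- Control, n = 800, λ = 0.05: 90.5 events. Program, λ = 0.035: 64.6 events. Total D ≈ 155.
- Power (Freedman) = Φ(√D × (1−HR)/(1+HR) − 1.96) = Φ(12.46 × 0.1765 − 1.96) = Φ(0.24) = 59.4%. The Schoenfeld form gives 60.3%. The protocol prints 59%.

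All nine cells of Table 3.3.7 (printed, then recomputed by Freedman):

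| Effect | 3%/yr | 5%/yr | 7%/yr |
|---|---|---|---|
| 20% | 20 / 19.9 | 30 / 29.5 | 39 / 38.3 |
| 30% | 40 / 40.6 | 59 / 59.4 | 73 / 73.0 |
| 40% | 66 / 65.9 | 86 / 85.6 | 95 / 94.3 |

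The largest gap is 0.7 points, with all 1,600 at risk. Other conventions (annual rate converted by −ln(1−r), fixed follow-up of 2.5 or 2.7 years, Schoenfeld instead of Freedman) move the 59% cell only between 56.7% and 61.4%.

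**Step 2: baseline cases excluded.** The number at risk and D shrink in proportion.

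| Assumed prevalence | At risk | Events | Power |
|---|---|---|---|
| 0% | 1,600 | 155 | 59.4% |
| 10% | 1,440 | 140 | 55.0% |
| 20% | 1,280 | 124 | 50.2% |
| 30% | 1,120 | 109 | 45.2% |
| 50% | 800 | 78 | 34.3% |

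**Step 3: baseline cases kept in.** Assume visits at 6, 18 and 30 months, 80% of baseline cases still positive at the next visit in both arms, and that those who resolve then carry the onset hazard of their arm. At 20% prevalence, per arm of 800:

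- *Month 6* (0.92^0.5 = 0.959 attending). Control probability of an event: 0.20×0.80 + 0.80×(1−e^−0.025) = 0.160 + 0.0198 = 0.180, or 137.9 events. Program: 0.160 + 0.80×(1−e^−0.0175) = 0.174, or 133.4 events.
- *Month 18* (0.92^1.5 = 0.882 attending). Control: 0.820×(1−e^−0.05) = 0.0400, or 28.2 events. Program: 0.826×(1−e^−0.035) = 0.0284, or 20.1 events.
- *Month 30* (0.92^2.5 = 0.812, times the 0.632 of participants followed that long, = 0.513). Control: 0.780×0.0488 = 0.0381, or 15.6 events. Program: 0.798×0.0344 = 0.0274, or 11.3 events.

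Totals are 181.7 and 164.8, a ratio of 0.91. Solving the Cox score equation over the three visits gives a hazard ratio of 0.90. Repeating this at 10, 30 and 50% prevalence gives about 0.85, 0.93 and 0.96.

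**Step 4: let the program also speed resolution.** At 20% prevalence, set program persistence to 70%. The month-6 probability becomes 0.140 + 0.0139 = 0.154 (118.1 events). With 20.5 and 11.5 events at the later visits the total is 150.1, and 150.1/181.7 = 0.83, against 0.91 in step 3. The dilution in step 3 therefore depends on the equal-persistence assumption.

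**The case against.** The strongest reply is that section 12.2 is silent, not wrong. The hypothesis speaks of incidence and Table 3.3.7 is headed by incidence rates, which points to new cases and hence to people free of disturbance at SV2. The baseline measurement needed for that restriction is taken. The cut-off that makes a score a disturbance, and the exact risk set, are details that a statistical analysis plan (not available here) commonly supplies. The aim is exploratory and the sample size does not rest on it.

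Much of this stands. A reader might infer that the Cox model is run in everyone, that most events would be prevalent cases, that the analysis cannot show improvement, and that power collapses to 6–20%. The documents do not support that reading:

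- Inclusion of everyone is inferred from silence and from the power table. It is not stated.
- If baseline cases were included, a participant whose disturbance resolved before month 6 would not be an event then, so improvement would move the hazard ratio, though mixed with onset.
- The collapse in power rests on a prevalence that the protocol does not give and on assuming that the program does nothing for existing disturbance. Step 4 shows how much that second assumption matters.

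What the reply does not remove is that the protocol itself fixes the hypothesis, the model and the power figure, and no single reading satisfies all three. A disturbance-free risk set leaves improvement unanalysed and the printed power too high. An all-inclusive one matches the power table's headcount but is not an incidence analysis.

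**Conclusion.** The point holds in a limited form. The improvement half of the sleep-wake hypothesis has no analysis that estimates it, although repeated scores are collected and ADL disability and ventilatory capacity receive baseline-adjusted mixed models. For the incidence half, the protocol states no disturbance-free risk set, and Table 3.3.7 makes no allowance for baseline cases, unlike MCI/D.

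The size depends on baseline prevalence, which is unknown. With baseline cases excluded, the 59% falls to about 55, 50, 45 or 34% at 10, 20, 30 or 50%. With them included and persistence equal at 80% per visit, an onset hazard ratio of 0.70 would appear as about 0.85 to 0.96 over the same range, and nearer to 0.70 if the program also speeds resolution. Because the outcome is tertiary and exploratory, no primary or secondary conclusion is affected. The change is worth making, but it is not critical.

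**What to change.** Split Tertiary Aims #4 in section 12.2:

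- **Incidence.** Keep the stratified Cox model, but limit it to participants without the disturbance in question at SV2. Restate Table 3.3.7 for the reduced number at risk over a range of assumed baseline prevalence, as step 2 does.
- **Improvement.** In all participants, add a repeated-measures model of the ESS, ISI and PSQI scores at 6, 18 and 30 months, adjusted for the SV2 score, field center and gender, on the pattern already planned for ADL disability and ventilatory capacity.

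The cost is a lower printed power for a tertiary outcome and a little more analysis. No new data are needed. Fixing the risk set before unblinding also removes a choice that could otherwise be made after the results are seen.
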